## Abstract

**Background:**

Total hip and knee arthroplasties significantly improve the quality of life for patients with severe osteoarthritis. However, some patients experience complications that require follow-up care. Amid rising demand for these arthroplasties, debates have emerged around the value of routinely scheduled follow-ups (RFUs). This qualitative study, nested within a hybrid effectiveness de-implementation trial that assesses quantitative differences between RFU and check-ups on-demand (COD), will explore and compare the patients’ and health care professionals’ (HCPs) experiences with, and perceptions about, RFU and COD at 1 and 10 years after total hip and knee arthroplasty.

**Materials and methods:**

First, a pre-study reference panel will be organised to prepare a focus groups topics guide. Subsequently, 2 methods of data collection will be used: 8 focus groups with total of 80 participants from the main trial and 10 in-depth interviews with different HCPs. Thematic analysis using a deductive approach will be performed on anonymised transcripts to identify key themes. For this, the comparative case study framework and the Theoretical Framework of Acceptability will be used. Findings will be used to inform the transition from RFU to COD if deemed acceptable by patients and HCPs.

## Introduction

Total hip arthroplasty (THA) and total knee arthroplasty (TKA) are effective and safe surgeries that improve quality of life for patients with severe osteoarthritis [1,2]. Radiographic follow-up studies have shown that between 0–3% of patients develop post-operative complications requiring further treatment or revision surgery within 6 weeks to 1 year after surgery [3,4]. These include dislocation, infection, osteolysis or periprosthetic fracture (e.g., [5–10]). While these complications occur relatively infrequently, their early identification is crucial [11] and this explains why most patients after THA and TKA are still scheduled for routine follow-ups (RFUs) in hospital. Despite expert support for these radiographs and follow-ups [12] based on low-level evidence information and guideline recommendations [13–17], there is little consensus on their overall value, optimal frequency, and timing, leading to considerable variation in clinical practice [18,19].

With rising total joint arthroplasty demand due to ageing [20,21] and increasing rates of obesity [22,23], hospitals face pressure work more efficiently to meet waiting list targets while maintaining budgets [19]. This has sparked debate among orthopaedic HCPs about the need for, and usefulness of, several of the scheduled RFUs [10,19,24,25]. There is mainly discussion around de-implementing follow-ups for patients with well-established prostheses [26]. After all, symptomatic complications beyond one year after the index procedure are infrequent [27,28], most symptomatic patients do not require surgical intervention and surgeons can effectively identify patients likely to experience prosthesis failure for follow-up [29]. Additionally, most complications are not even detected during RFUs, but rather during unplanned hospital visits [25,30,31]. Repeated, uneventful follow-up visit can lead to frustration for both patients and orthopaedic HCPs [19]. Refraining from these can save costs [32–34], reduce CO_2_ emissions [33,35] and may reduce hospital wait times and wait lists.

While both patients and HCPs acknowledge the benefits of reducing in-person RFUs in terms of patient convenience and resource allocation, concerns remain about missing the opportunity to detect harmful issues with arthroplasties before irrevocable damage occurs [18,19]. Disinvestment in follow-ups may also weaken the human connection central to clinical care, contributing to both patient and HCP dissatisfaction [19,34,36] even though patients have also indicated they found reduced or alternative follow-up methods satisfying (e.g., [32,33,37,38]). Despite ongoing debate and a lack of high-quality evidence, many hospitals have already decided to reduce or even eliminate follow-ups [10,19,39].

Before RFUs after THA and TKA are de-implemented, it is crucial to understand what patients and HCPs find important in this regard for reasons of safety, quality of care and respecting patient preferences. Qualitative research is well-suited for exploring such perceptions [40]. A previous qualitative interview sub-study explored views of professional leads and service managers of orthopaedic hospital departments about implementing new care pathways such as de-implementing follow-ups for patients after THA and TKA [19,41]. Although interviewees felt that ‘traditional’ follow-ups frequently offered little benefit to the patient and suggested that a more meaningful form of follow-up should be adopted, the views of patients themselves nor the HCPs conducting these visits were explored. Experiences and perceptions of both patients after THA and TKA and two of their clinicians were evaluated in a transition from a traditional follow-up clinic to a virtual clinic pathway [34]. This transition was well accepted overall, but both groups agreed that patients with concerns or symptoms should have easy access to face to-face review, regardless of when these concerns or symptoms occur. To our knowledge, research on transitioning from a routinely scheduled follow-up regimen to a demand-driven follow-up regimen which allows patients and HCPs to seek follow-up only as needed, at their discretion, has yet to be conducted. This protocol paper outlines a qualitative study within a hybrid effectiveness de-implementation trial which will explore the experiences and perceptions of patients and HCPs regarding both RFU and check-ups on-demand (COD), and assess COD acceptability.

## Methods and materials

### Design and objectives

This qualitative study is nested within a large nationwide hybrid effectiveness de-implementation trial (https://projecten.zonmw.nl/nl/project/standaardcontroles-na-een-totale-heup-knieprothese-verspilde-moeite-passende-zorg-haka) conducted in 10 non-academic hospitals in the Netherlands. A large group of stakeholders co-created this trial and secured a grant intended for studies aimed at investigating and improving the efficiency and cost-effectiveness of specialized medical care (https://www.zorgevaluatienederland.nl/evaluations/haka-1-year-fu and https://www.zorgevaluatienederland.nl/evaluations/haka-10-year-fu). The SPIRIT Schedule of Enrollment, Interventions, and Assessments (Fig 1) was adapted to summarise the 3 separate work packages of this trial. The qualitative work package (protocol version 1.0 of 14 February 2025) was granted a waiver of ethical approval on March 19, 2025 by the Leiden-Den Haag-Delft Medical Research Ethics Committee (reference number N25.014) and registered on 19 June 2025 (Clinicaltrials.gov ID: NCT07041528, https://clinicaltrials.gov/study/NCT07041528). The nationwide main trial is expected to start in July 2025, with the first qualitative work package activities commencing thereafter.

**Fig 1 pone.0330652.g001:**
[figure not shown]
Adapted SPIRIT Schedule of Enrollment, Interventions, and Assessments summarising all 3 work packages of the nationwide hybrid effectiveness de-implementation trial. a This part of the study recruits patients scheduled for total hip or knee arthroplasty. A staggered crossover process is used whereby each of the 10 participating hospitals/sites – in a randomised order – sequentially closes recruitment for RFU and (after a two-month transitioning phase) initiates recruitment for COD. b During WP1 and WP2 assessments, outcomes include PROMIS physical function, healthcare consumption (clinical visits, radiographs), the number and type of complications and surgical interventions, health related quality of life, pain, satisfaction and healthcare costs. c This part of the study recruits patients who had total hip or knee arthroplasty 10 years ago. Only the RFU and Active COD cohorts will be assessed. For a Passive COD cohort, only retrospective registry data will be collected. d Participants are enrolled in WP2 approximately 10 years after undergoing total hip or knee arthroplasty. Therefore, the time points referred to as “3-month”, “6-month”, and “1-year” assessments should be understood as 10 years + 3 months, 10 years + 6 months, and 11 years after surgery. These labels reflect the time elapsed since enrolment in this follow-up phase, not since the original procedure. COD, check-up on demand; HCP, health care professional; RFU, regular follow-up; WP, Work Package.

New patients planned for THA or TKA surgery (work package 1) and patients having had their THA or TKA index surgery 10 years ago (work package 2) will receive RFU or COD. The trial’s main work packages 1 and 2 will investigate the difference in effect between RFU and COD regimens on physical functioning, post-operative complications, quality of life, pain and healthcare consumption at selected time-points after the index surgery. Subsequently, this qualitative study (work package 3) will explore and compare the patients’ and HCPs’ experiences with, and perceptions about, the two different ‘cases’ of RFU and COD using the comparative case study framework [42]. In particular, the concurrent acceptability of the COD regimes will be explored using selected component constructs of the Theoretical Framework of Acceptability [43]. Two methods of data collection will be used: focus groups with participants and in-depth interviews with HCPs. Prior to conducting these, a pre-study reference panel will be organised to prepare the focus groups topics guide.

### Consent

All participants will first provide written informed consent to take part in either the main trial’s 1-year or 10-year follow-up study. Within the consent form, participants can indicate their willingness to participate in a focus group. Participants selected for focus group participation will additionally be asked to sign a separate informed consent form. Reference panel members will also be asked to provide verbal consent to be consulted, and HCPs will be asked to provide written informed consent to be interviewed.

### Patient and public involvement: Pre-study reference panel

Before any focus groups are conducted, we will recruit 10 people [44] with lived experience of THA and TKA surgery through network contacts within non-profit patient advocacy organizations for people with rheumatic conditions (ReumaZorg Nederland) and osteoarthritis (Poly-Artrose Lotgenoten Vereniging). In the second half of 2025, these people will be invited to share their experiences with post-operative follow-ups and will be asked to assist the researchers in formulating appropriate, actionable, clear, precise and relevant open-ended questions for the focus groups.

During a 2-hour meeting, researchers will first frame the aim and procedures of the reference panel [44]. After the panel members have been asked about their background and about their experiences with THA or TKA surgery and hospital follow-ups, they will receive evidence-based information about the main drivers of acceptability of, and patient satisfaction with, clinical services. Subsequently, the panel members’ feedback will be sought on a tentative focus group topics guide prepared by the researchers. During this process, panel members will be asked if any additional themes need to be explored, and to formulate open-ended questions for these. During a second 1-hour meeting, and until group consensus is reached, the researchers will seek the panel members’ feedback on a refined interview topics guide, and ensure that all questions are easy, clear, and understandable.

### Focus groups

A purposive sample of 80 participants who completed the main trial’s 1-year or 10-year follow-up studies will be approached and recruited for the post-intervention focus groups. Comparing these participants’ experiences and perceived satisfaction with their respective follow-up regimens will help determine if de-implementing RFU and adopting COD is acceptable.

Participation in the focus group is only possible for participants with a good command of the Dutch language. Participant sampling will further be based on variation in gender, age, traveling distance to the hospital and the American Society of Anesthesiologists (ASA) physical status classification. We will also strive to include participants who have had revision arthroplasty during participation to ensure that their perspectives are also captured for reasons of data adequacy [45,46]. A total of 8 focus groups of approximately 60–90 minutes will be conducted between January 2027 and April 2028, each consisting of 10 participants. Four focus groups will be organised for participants in the 1-year follow-up study, covering the following categories: THA with RFU, THA with COD, TKA with RFU, and TKA with COD. Similarly, 4 focus groups will be organised for participants in the 10-year follow-up study. All focus groups will be attended by at least 1 experienced qualitative researcher and 1 junior researcher, with each either moderating the discussions or taking field notes. All focus group venues will be easily accessible in terms of parking, physical access and public transport. Focus group participants will receive a 25-euro reimbursement for their travel and parking expenses.

A mix of semi-structured open-ended focus group questions will primarily be structured around themes that have emerged during previous research aimed at evaluating factors that influence patient satisfaction in general, and with medical consultation in particular. These studies have shown that interpersonal factors dominate perspectives of patient satisfaction [47]. An important theme in this regard is communication between caregivers and patients [47–50], for example communication about medical information that patients need or receive during a follow-up visit. Patients’ perceptions about being listened to, being heard or being helped by the provider can be captured under the theme of empathy [47,51,52] while trust has also been identified as a primary driver of patient satisfaction with clinical services [47,53]. Patients’ expectations also influence their degree of satisfaction [47,49,54]. Clinic environmental factors can also play a role such as the clinics’ responsiveness and easy accessibility [48] when patients request an appointment or the amount of clinical contact time [47,50,55,56] available to ask questions and address the patients’ concerns. Participants will be asked about perceived health risks (‘safety’) with, barriers and facilitators of, likes and dislikes about, and recommendations for alternative models of RFU and COD. To understand if the follow-up regimens are acceptable to patients, some additional questions will also be structured around the seven component constructs of the Theoretical Framework of Acceptability (v2) [43,57]. One question will ask participants about their fear-avoidance beliefs to help gauge the effectiveness of RFU and COD in terms of patient concerns or reassurance. Another question will explore whether—and why—patients’ satisfaction with their prosthesis is related to their preference for scheduled RFUs or COD. Additional questions may arise based on input from the pre-study reference panel.

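### Focus-group sampling does not select on whether a COD participant ever requested a check-up, so a COD group may hold nobody who can describe on-demand access from experience

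*Protocol article*

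**What the plan says.** The Focus groups section plans the sample as follows: "A purposive sample of 80 participants who completed the main trial’s 1-year or 10-year follow-up studies will be approached and recruited". The layout is fixed: "A total of 8 focus groups of approximately 60–90 minutes will be conducted between January 2027 and April 2028, each consisting of 10 participants". The four groups of the 1-year study are set out as "covering the following categories: THA with RFU, THA with COD, TKA with RFU, and TKA with COD", and the 10-year study follows the same pattern. Four of the eight groups are therefore COD groups.

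Within those strata, "Participant sampling will further be based on variation in gender, age, traveling distance to the hospital and the American Society of Anesthesiologists (ASA" physical status class). Good Dutch is required. The next sentence adds an aim, without a number and not tied to any regimen, to include people who had a revision during participation.

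The topics listed in the same section include the clinic's "responsiveness and easy accessibility [48] when patients request an appointment", alongside trust, empathy, expectations, perceived safety, and likes and dislikes.

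The Fig 1 legend lists among the outcomes of work packages 1 and 2 "healthcare consumption (clinical visits, radiographs), the number and type of complications and surgical interventions". The Introduction says that between 0 and 3% "of patients develop post-operative complications requiring further treatment or revision surgery within 6 weeks to 1 year after surgery". The In-depth interviews section sets an exposure minimum for professionals: they must have cared for at least 3 trial participants. Patients have no comparable rule.

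**The concern.** COD differs from routine follow-up (RFU) in that the patient has to ask for a check-up. Whether asking works (how easily a visit is obtained, how quickly, and whether the concern is dealt with) can be described first-hand only by someone who has asked. The Introduction and the Discussion both treat access when needed as the condition on which patients accept reduced follow-up. The Discussion says the study may show whether that acceptance extends to a demand-driven model.

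The stated sampling variables are demographic, geographic and general-health characteristics. None is chosen to bring in users, and the only event-based aim covers revision, the severe end. A COD group could therefore meet every stated criterion and still contain no user. Its views on access would then be expectations rather than experience. Because each joint-by-cohort category has a single COD group, no second planned group would make up for it.

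**Working it through.** **The plan's own figure.** 8 groups × 10 participants = 80, which matches the stated sample. COD groups: 2 in the 1-year study + 2 in the 10-year study = 4, so 4 × 10 = 40 COD participants, 20 of them in the 1-year study.

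**Input not in the document.** The share *p* of COD participants who request at least one check-up is not given. I assume 5% to 30%, with 50% as a favourable extreme, and treat selection as unrelated to use because no stated criterion selects on it directly.

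**Formulas.**
- No user in a group of 10: (1 − p)^10
- At least one of the 4 COD groups without a user: 1 − [1 − (1 − p)^10]^4
- No user among all 40: (1 − p)^40
- At most one user in a group of 10: (1 − p)^10 + 10p(1 − p)^9

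| Assumed use | No user in 10 | At least 1 of 4 groups without a user | No user in 40 | At most 1 user in 10 |
|---|---|---|---|---|
| 5% | 59.9% | 97.4% | 12.9% | 91.4% |
| 10% | 34.9% | 82.0% | 1.5% | 73.6% |
| 20% | 10.7% | 36.5% | 0.01% | 37.6% |
| 30% | 2.8% | 10.8% | below 0.01% | 14.9% |
| 50% | 0.1% | 0.4% | below 0.01% | 1.1% |

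Example at 10%: 0.90^10 = 0.349, and 1 − (1 − 0.349)^4 = 0.820.

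**Complications.** The Introduction's upper rate is 3%. It covers 6 weeks to 1 year and only events needing further treatment or revision, so I apply it to the 20 one-year COD participants and not to the 10-year groups. With untargeted selection, 0.97^10 = 0.737 is the chance that one group has no such case, and 0.97^20 = 0.544 that neither one-year COD group has one. At 1%, the same figures are 0.99^10 = 0.904 and 0.99^20 = 0.818. Because revisions are sought, these figures describe the plan without that aim. Complications short of revision are only part of the 3% and are not sought at all.

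**Pool needed for a minimum of 2 to 3 users.** The expected number of volunteers to screen per category is 2/p to 3/p: 40 to 60 at 5% use, 20 to 30 at 10%, and 10 to 15 at 20%.

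**The case against.** Several counter-arguments have force.

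- **Not calling is part of COD.** The Introduction describes follow-up sought only when needed. A reader might infer that a group of non-users has not experienced the regimen at all. The document does not support that: an uneventful course without a check-up is COD as designed, and non-users can speak on trust, safety, reassurance, expectations and preferences. Strengths and limitations even mentions a final clinical visit for COD participants, without saying whether it was on demand. This stands, and it limits the point to access on request and to problems that arise.
- **Complications are not ignored.** Revision cases are sought explicitly. This stands, but the aim has no minimum, is not tied to the COD groups and leaves out lesser complications.
- **Non-users will approve of COD by construction.** This too might be inferred, but nothing shows it. The Introduction itself says that less follow-up may weaken human contact and leave patients dissatisfied.
- **The unit is too small.** RFU and COD transcripts are analysed as two cases, so the 40 COD participants together matter most, and a total absence of users is unlikely once use reaches 10%. This stands for the overall contrast, but not for statements about one joint or one cohort.
- **Selection is not random.** Volunteers may hold stronger views, and revision cases will have had extra care. Either could raise the share of users, by an unknown amount.
- **Other sources cover safety.** Work packages 1 and 2 measure complications, and professionals are interviewed on safety. Neither gives the patient's account of seeking access. Groups can be added until saturation, but nothing says that they would be sampled differently, and a set of non-users can saturate on non-user views.
- **This is a condensed article.** A full protocol exists and may say more. However, the article does list its sampling variables, and the point concerns that list.

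A reader might also infer that hospital is confounded with regimen because COD arrives hospital by hospital. The Fig 1 legend does not support this for newly operated patients: each of the 10 hospitals recruits first to RFU and then to COD.

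**Conclusion.** The point holds in a limited form. It is a design weakness in the sampling criteria, and the document does not contradict itself. Nothing in the stated criteria secures COD participants who requested a check-up or had a complication short of revision, although access on request is a planned topic and central to whether COD is acceptable.

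The size depends on a use rate that the document does not give. At 20% use or less, a group without a user is a realistic prospect (11% to 60% per group). At 30% it is unlikely for any one group (3%), and at 50% negligible. These figures assume that selection is unrelated to use. They do not show that the COD evidence as a whole would lack users, that COD would be judged acceptable automatically, or that safety would go unexamined. The change is worth making because it is cheap before the groups start in January 2027 and hard to make good afterwards.

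**What to change.** In the Focus groups section, add two sampling variables for the four COD groups:

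1. Whether the participant requested at least one on-demand check-up.
2. Whether the participant had any complication or unscheduled visit, not only a revision.

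State a modest minimum of users per COD group, for example 2 to 3 of 10 as far as available, and keep non-users represented. The number is a judgement, not a derived figure. Apply the same criteria to any group added under the saturation rule, and report the number of users in each COD group so that readers can weigh the statements on access.

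The information can come from the visit and complication data of work packages 1 and 2. The team should check that those records distinguish visits the patient asked for from other visits. A fixed half-and-half split and quotas by hospital are not needed.

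The cost is a sentence or two of protocol wording and one data query per group. Invitations become more selective and groups fill somewhat more slowly, most of all if use is near 5%. The 8 groups and 80 participants do not change.
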